## Abstract

**Simple Summary:**

Falls in community-dwelling individuals aged over 65 produce serious outcomes such as disability, morbidity, and mortality, as well as high healthcare costs. This research aims to assess whether a multicomponent training programme (McTP) combined with a transcranial direct-current stimulation device (tDCS), Halo Sport, produces improvements in balance and other gait-related parameters. Therefore, this study intends to test the efficacy of adding a tCDS device to an McTP in order to prevent falls in older adults by testing the safety, efficacy, and effectiveness of its implementation in care resources for the elderly.

**Abstract:**

Approximately one-third of elderly people aged over 65 who live in the community experience falls every year, with the proportion increasing with age. Moreover, of those who fall, about half will fall again in the following year. The falls’ consequences include disability, morbidity, and mortality. Although many external and internal factors lead to falls, balance issues play a major role. Multi-component training programs (McTP) usually combine balance, strength, cardiorespiratory fitness, and flexibility, with studies reporting multiple benefits on the health-related quality of life. Halo Sport is a transcranial direct-current stimulation (tDCS) device with promising results for gait performance. This study aims to test the effectiveness of the introduction of a tCDS device to an McTP to prevent falls in older adults. The sample will consist of 46 people aged 65 years or older, randomly assigned to experimental (n = 23) and control (n = 23) groups. The experimental group will perform the McTP while wearing tDCS, and the control group will perform McTP without the device, for three sessions per week over 12 weeks. The main measures will provide information about (1) safety, (2) applicability, (3) balance, (4) number of falls, (5) physical fitness, (6) risk of falling, (7) fear of falling, (8) health-related quality of life, and (9) cognitive function. Among the practical implications of this program, it is intended to provide data on its safety and effectiveness to be implemented in different resources as a tool for the prevention of falls.

## 1. Introduction

Ageing involves a series of complex changes that affect individuals in their physical, cognitive, emotional, and social areas. The biological mechanisms that cause ageing occur differently in each person, but the way in which a person ages depends not only on particular biological aspects but is also influenced by the person’s environment and behaviour, such that programs to address the health, quality of life and psychosocial aspects of older adults must be implemented [1]. Ageing is associated with changes in the endocrine, cardiovascular, respiratory, neurological, gastrointestinal and musculoskeletal and sensory systems [2], which may lead to a decline in functional capacity [3].

Falling is the result of a multiple-factor interaction that causes the individual to be unable to maintain or regain balance [4]. Falls are multifactorial; thus, biological, behavioural, social, economic, and environmental risk factors derived from community factors must be considered [5] (i.e., intrinsic and extrinsic factors [6]). A major contributor is balance, which can be defined as “a multidimensional concept, referring to the ability of a person not to fall” [7,8]. Estimates suggest that 13% of those aged 65–69, and up to 46% of those over 85, experience balance problems [9]. Balance is required in order to maintain a posture, perform voluntary movements, and react to external disturbances; individuals must be able to keep their centre of mass within their support base, with this skill being influenced by ageing [10].

Falls are frequent and particularly disabling [11], being one of the primary causes of mortality and morbidity in older adults [12,13]. Their consequences include fractures, bruising, lacerations, and sprains at a physical level [5], and a self-confidence loss and fear to fall again as common psychological symptoms, impacting the social and economic spheres, and affecting the quality of life [14]. Falls have become a serious public health problem because their consequences increase healthcare costs ($50 billion in the United States of America) [15].

Although falls are often considered to be part of the “normal ageing process”, they can be prevented [16]. Thus, multidisciplinary fall prevention programs should be implemented. Among the different types of interventions, exercise training has been shown to be effective [17,18,19]. However, the components of the programs influence the results. Different studies indicate that programs of which the main components were balance and functional tasks reduced falls rate by 24%, while those that included the categories included in the Prevention of Falls Network Europe taxonomy (ProFANE) [20], decreased the rate of falls by 34% [21]. The World Health Organization (WHO) [22] and the American College of Sports Medicine (ACSM) [23] recommend interventions that train physical capacities, recommending multi-component training programs (McTP) which involve strength, cardiorespiratory endurance, flexibility and balance training, as they have reported multiple improvements in functional capacity and health-related quality of life, and a lower rate of falls and cognitive impairment [24]. In the same line, the Spanish Ministry of Health recommends McTP that includes cardiopulmonary endurance, strength, power and functional capacity, flexibility, and balance training [25,26,27].

Non-invasive electrical brain stimulation (NIBS) is a promising and versatile technique used to study brain function and treat neurological and neuropsychiatric diseases [28]. Within the NIBS device typology, transcranial direct-current stimulation (tDCS) is a non-intrusive and painless brain stimulation technique that consists of the application of direct electrical currents to stimulate specific brain segments [29], differentiating two types of stimulation: anodal, to excite neuronal activity, and cathodal, to inhibit or reduce it [30]. Moreover, tDCS have generated great interest in areas such as cognitive functions and motor and physical performance [31,32]. The tDCS can stimulate neuroplasticity becase it modulates changes in neuronal membrane potential and produces an increase in cortical excitability [28]. Some works indicate that tDCS facilitates long-term potentiation by depolarizing the membrane potential, resulting in better motor learning, leading to possible gait performance improvements [33,34,35,36] and fall prevention. Halo Sport, a few years ago, marketed a device to improve physical performance based on tDCS [37]. It is a portable, easy-to-use, low-cost device consisting of a headset with an integrated tDCS headband that provides a weak direct current (DC) of below 2–3 milliampere (mA). It can be worn for up to 20 min. Surface electrodes, known as primers, are placed on the scalp to induce changes in both motor cortex sides [38], as they generate neural impulses for movement execution [39]. Halo Sport produces changes in motor cortex excitability, improving motor performance. One possible mechanism for this effect is that tDCS increases the intracortical facilitation of the motor cortex excitability, permitting these neurons to make new connections easily, improving skeletal muscle motor drive [40]. If gait performance is improved, benefits could include better mobility and a reduced fear of falling [41].

We aim to study whether the association of a multi-component training program (McTP) combined with transcranial direct-current stimulation (tDCS) device (Halo Sport) is safe, applicable, and can enhance performance on gait and balance. Additionally, this project has a secondary aim to evaluate the effect of the combined program on the falls, physical fitness, health-related quality of life, and cognitive function of participants, and the safety and applicability of the program. We hypothesize that the group that performs the McTP combined with tDCS will obtain better results in the primary variable, balance, as well as in the secondary variables.

## 2. Materials and Methods

### 2.1. Study Design

A randomized controlled trial will be conducted with a 1:1 assignment ratio between the experimental and control groups. The Consolidated Standards for Reporting Trials will be followed (CONSORT) [42].

### 2.2. Ethics and Registration

This study has been approved by the Bioethics and Biosafety Committee of the University of Extremadura (approval number: 184/2021). Moreover, the study has been registered in the Clinical Trials Registry provided by the Australian New Zealand Clinical Trial Registry (Request number: 383356; https://www.anzctr.org.au/ (accessed on 9 October 2021)).

### 2.3. Sample Size

The sample size was estimated based on the Time Up and Go (TUG) test results in older people, a test which is considered valid and reliable for this population [43,44]. Thus, accepting a risk alpha of 0.05 and a risk beta of 0.2 in a bilateral contrast, a total of 44 individuals (22 both in the experimental and control group) are needed in order to find a difference equal to or higher than 0.97 units. A common standard deviation of 1.3 and a correlation coefficient between the baseline and end-line measurement of 0.7 are assumed [45]. A loss of follow-up rate of 20% is predicted.

### 2.4. Randomization and Blinding

After the initial assessment, a simple computer-generated randomisation sequence will be generated to assign the participants (1:1) to the experimental (McTP + tDCS) and control (McTP) groups using Research Randomizer software (Version 4.0, Geoffrey C. Urbaniak y Scott Plous, Middletown, CT, USA; http://www.randomizer.org, accessed on 15 September 2021) [46]. A researcher not involved in the study will prepare the randomization sequence. This information will be hidden in a password-protected file. Both the participants and professionals who will lead the sessions will be aware of their group allocation; however, it will be hidden from the data analysis investigators.

### 2.5. Eligibility Criteria

The participants will comply with the following inclusion criteria: (a) age ≥ 65 years old; (b) not suffering any pathology that contraindicates physical activity(the Physical Activity and Fitness Questionnaire (PAR-Q) will be run) [47]; (c) not presenting signs of cognitive impairment based on the Mini-Mental State Examination (scores > 25) [48]; (d) not presenting contraindications to tDCS use; (e) participants must provide to the researchers a signed informed consent form; and (f) they must show motivation to participate in the program. Moreover, the exclusion criteria will include: (a) living in a nursing home; (b) needing an assistive device to move or walk; (c) having any of the lower limbs amputated; or (d) presenting sensorial impairment that makes the normal development of exercise difficult.

### 2.6. Intervention

#### 2.6.1. The Multicomponent Exercise Program

Before starting the first training session, the participants will receive an explanation of the protocol to follow. The program will be composed of 3 sessions (30 min) per week over 12 weeks. Each session will be supervised by experts in the field. The structure of the sessions will consist of a 10-min warm-up (joint mobility, stretching), a 20-min main part of McTP exercises or activities wearing the Halo, and a 10-min cool-down (stretching, final thoughts and personal hygiene). The participants will wear the Halo only during the main part (20 min). The McTP will consist of balance, strength, cardiorespiratory endurance, and flexibility exercises, with several of these components being trained in each session. Examples of the activities are provided in Table 1. Furthermore, each participant will be asked for the Rating of Perceived Exertion [49] at the end of each session in order to monitor the intensity of the session.

The McTP includes gradual increases in exercise intensity, volume and complexity, together with accompanying balance, strength, endurance and flexibility exercises [25]. 

#### 2.6.2. Experimental Group

The experimental group will perform the McTP while wearing the Halo Sport (Halo Neuroscience, San Francisco, CA, USA; https://www.haloneuro.com, accessed on 9 October 2021), a commercial tDCS device which is similar to audio headphones. Three-pointed foam electrodes (24 cm^2^/primer), moistened before use, will make electrical contact with the head. The Halo Sport will be placed on the vertex of the head after cleaning the stimulation area with alcohol swabs, and the integrated electrodes of the device will be saturated with water. The primers are located on the upper head to stimulate both sides of the motor cortex. The electrodes are linked to a DC electrical stimulator, powered by a lithium-ion cell (LiPo 36 V). The anodal electrode is positioned on the top of the head, and the cathodal electrodes on the left and right sides. The current of the anodal tDCS will be set at 2 mA for 20 min [50], and will be monitored by the Halo Sport app in a mobile device [51,52]. The participants will remain seated in a resting state while the Halo Sport headphones are placed on them, and will perform the exercises while equipped with the device. 

#### 2.6.3. Control Group

Participants will perform the McTP program without the tDCS stimulation. 

Both the experimental and control groups will participate in the initial, mid-term and final evaluations.

### 2.7. Measures and Procedures

Before taking any measurements, a test familiarisation session will be conducted with the participants. A set of evaluation tests will be applied to evaluate the program’s usefulness and effectiveness through initial, mid-term and final assessments, as shown in Table 2.

#### 2.7.1. Primary Measures

Balance will be assessed using the TUG [43,44], and the Activity-Specific Balance Confidence Scale (ABC) [7,53,54] will be performed. The 3-metre variant of the TUG will be performed. The participant, sitting in a chair, with arms and trunk resting on the backrest, stands up on the investigator’s signal and walks in a straight line, turns 180 degrees, walks back, and sits back down in the chair as fast as possible. Before recording the measurements (there will be two attempts with a one-minute break), a familiarisation test will be performed. The time will be measured from the start of the standing movement until the participant sits down again with his/her back against the backrest. The data from the best attempt will be taken for analysis. The ABC questionnaire is a 16-question tool that assesses the confidence a person has in their balance when carrying out daily activities, with scores ranging from 0 to 100. A score of more than 67% is considered to be a high risk of falling.

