### 2.8. Statistical Analysis

The statistical analysis will be conducted through the Statistical Package for the Social Sciences software (SPSS, Version 25, IBM SPSS, Armonk, NY, USA).

The characteristics of the study participants will be presented as the mean (standard deviation) and proportions for continuous and categorical variables, respectively. We will carry out an intention-to-treat (all participants), and a per-protocol analysis (individuals who complete the program).

Intention-to-treat analysis: All of the randomised participants will be considered for the analysis in their relevant group. Missing data will be imputed through multiple imputations. Repeated measures analyses of covariance (ANCOVA) adjusted by age and baseline outcomes will be applied to analyse the intervention effects on the different dependent variables. The baseline outcomes will be applied as a covariate for all of the dependent variables’ pre–post-comparisons in order to avoid the bias of possible differences between the groups in the initial outcomes. The effect sizes (95% confidence interval) and differences for each variable concerning the time and the group × time interaction will be calculated. The alpha level will be set at *p* < 0.05. The data imputation for the sensitivity analyses will be conducted on patients who presented data at the baseline, and who completed the study, in order to avoid estimation bias.

Per-protocol analysis: The analyses previously described will be carried out but considering only those participants who attended at least 75% of the program sessions.

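### Balance is the one primary variable, but it has two unranked primary measures (TUG and ABC), only TUG is powered, and nothing says how the two results decide the primary claim

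*Protocol article*

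**What the plan says.** Four places in the protocol article bear on this.

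- **Introduction, aims and hypothesis.** The combined-programme group "will obtain better results in the primary variable, balance, as well as in the secondary variables". One primary variable is named, as a construct.
- **Section 2.7.1, Primary Measures.** "Balance will be assessed using the TUG [43,44], and the Activity-Specific Balance Confidence Scale (ABC) [7,53,54] will be performed". TUG is a timed performance test. ABC is a 16-item self-report of confidence, scored 0 to 100. Neither is placed ahead of the other, and they are not combined.
- **Section 2.3, Sample Size.** "The sample size was estimated based on the Time Up and Go (TUG) test results in older people", "accepting a risk alpha of 0.05 and a risk beta of 0.2 in a bilateral contrast". ABC does not enter the calculation.
- **Section 2.8, Statistical Analysis.** Repeated-measures ANCOVA "will be applied to analyse the intervention effects on the different dependent variables", and "The alpha level will be set at *p* < 0.05". No division or ordering of alpha appears.

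**The concern.** The sample size spends one alpha of 0.05 on one test, TUG. The outcome section gives the primary label to two tests, and the analysis section gives one unadjusted alpha for all dependent variables. These statements do not fit together: a reader cannot tell which result, or which combination of results, would confirm the primary hypothesis.

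The gap matters most if the two measures disagree, which is plausible because one records performance and the other confidence. With TUG null and ABC positive, the text would not prevent a report of better balance. That report would rest on the measure for which no power was calculated. Section 3 links a demonstrated improvement in balance to wider use of the device in fall prevention, so the primary claim has practical weight.

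**Working it through.** **Inputs from the protocol article**
- Section 2.3: two-sided alpha 0.05, beta 0.2, difference 0.97, SD 1.3, baseline to end-line correlation 0.7, 20% loss, result 22 per group (44 in total).
- Section 2.7.1: two primary measures.
- Section 2.8: alpha 0.05.
- Not given: the correlation ρ between the TUG and ABC test statistics. It is an assumption here and is shown over a range.

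**Step 1. Reproduce the stated sample size**

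SD of change = 1.3 × √(2 × (1 − 0.7)) = 1.007.

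n per group = 2 × (1.960 + 0.842)² × 1.007² / 0.97² = 16.9, rounded up to 17.

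With 20% loss: 17 / 0.80 = 21.25, rounded up to 22.

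This matches the stated 22 per group. The figure is a single comparison of TUG change from baseline to the end of the programme, at the full 0.05, with the loss already included.

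**Step 2. Error rate if either measure suffices**

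With no true effect on either measure:

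P(at least one false positive) = 1 − P(|Z₁| < 1.96 and |Z₂| < 1.96), where Z₁ and Z₂ are standard normal with correlation ρ.

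At ρ = 0 this is 1 − 0.95² = 0.0975.

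| Assumed ρ | Chance of a false primary claim |
|---|---|
| 0 | 9.75% |
| 0.3 | 9.5% |
| 0.5 | 9.1% |
| 0.7 | 8.35% |
| 0.8 | 7.8% |
| 0.9 | 7.0% |

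**Step 3. If both measures must succeed**

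The error rate is then at most 5%. Joint power cannot exceed the smaller of the two powers, so it is at most the 80% planned for TUG. As an illustration only, suppose ABC also had 80% power. Independent tests would give 0.80 × 0.80 = 64%, and positive correlation would move this towards 80%. The protocol gives no ABC effect or SD, so the real figure cannot be computed.

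**Step 4. Two ways to control the error**
- *TUG first, then ABC only if TUG succeeds, each at 0.05.* The error rate over the two tests is at most 5%, and 22 per group still applies.
- *Bonferroni, 0.025 each.* The error rate is 1 − 0.975² = 4.94% if independent. For TUG, n = 2 × (2.241 + 0.842)² × 1.007² / 0.97² = 20.5, rounded up to 21 evaluable. With loss, 21 / 0.80 = 26.25, rounded up to 27 per group. With only 17 evaluable per group, TUG power would be 71%.

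**The case against.** The strongest reply is that decision rules, test order and multiplicity adjustment often sit in a statistical analysis plan, that none is shown, and that a journal article condenses. This stands to the extent that a missing adjustment alone would be no finding. It does not dispose of the point, because the article itself fixes two primary measures, one powered measure and one alpha, and these do not agree.

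A second reply is that TUG is implicitly the lead measure because it drives the sample size. That is a fair reading, and under it the primary error rate is 5%. But section 2.7.1 gives ABC the same primary status, so the reading needs to be written down.

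Three stronger readings are tempting and are not supported:

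- **That the plan runs a false-positive rate of 9–10%.** No section says a win on either measure is enough. The hypothesis speaks of one variable assessed by both instruments, so requiring both is equally open. Even on the either-suffices reading, the rate depends on a correlation that the document does not give.
- **That weeks 6 and 12 open further routes to success.** Table 2 schedules balance at both visits, but section 2.8 plans a repeated-measures analysis reporting a group × time interaction. It does not plan separate visit tests, each able to carry the claim.
- **That the lack of blinding adds to the inflation.** Section 2.4 says participants know their allocation, and ABC is self-reported. That is a question of bias: it does not enter the figures above, and no alpha rule would remove it. It is only a further reason not to let ABC carry the claim alone.

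**Conclusion.** The point holds in conditional form. What is certain from the text is the mismatch: one primary variable, two unranked primary measures, a sample size for one of them, and a single unadjusted alpha. What follows depends on a rule that the protocol does not give:

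- Either measure sufficient: about 7–10% instead of 5%, over assumed correlations from 0.9 down to 0. This takes section 2.8 in its natural sense, each variable tested at 0.05.
- Both required: no inflation, but the stated 80% power does not cover the joint claim.
- TUG alone decisive: 5% and 80% as planned, but ABC then does not belong among the primary measures.

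This should be settled before analysis. It does not call the sample size calculation into question, since that reproduces exactly for TUG.

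**What to change.** In section 2.7.1, name TUG at week 12 as the sole primary outcome, in line with the baseline to end-line basis of section 2.3, and test it at two-sided 0.05. Make ABC the first secondary outcome, tested at 0.05 only if TUG is significant. Label the remaining outcomes as supportive. Carry the same wording into the hypothesis in the Introduction and into section 2.8.

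The cost is wording and no extra participants: 22 per group stands, whereas keeping both measures as primary with a Bonferroni split would call for 27. The real concession is that a positive ABC result can no longer support the primary claim alone. Section 2.2 reports that the trial is registered, so the registered primary outcome may need a matching update; the registry record was not available to check.

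If the investigators want both measures to count, they can require both, or split alpha, and say so. They should then restate the power for the rule they choose.
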